**Methods:**

Prospective cohort study involving 13 hospitals in Spain with a follow-up period of up to 5 years after diagnostic biopsy. Eligibility criteria: Patients diagnosed with breast cancer between April 2013 and May 2015 that have consented to participate in the study. Data collection: Data will be collected on the following: pre-intervention medical history, biological, clinical, and sociodemographic characteristics, mode of cancer detection, hospital admission, treatment, and outcomes up to 5 years after initial treatment. Questionnaires about quality of life (EuroQoL EQ-5D-5 L, the European Organization For Research And Treatment Of Cancer Core Quality Of Life Questionnaire EORTC QLQ-C30 join to the specific breast cancer module (QLQ-BR23), as well as Hospital Anxiety and Depression Scale were completed by the patients before the beginning of the initial treatment and at the end of follow-up period, 2 years later. The end-points of the study were changes in health-related quality of life, recurrence, complications and readmissions at 2 and 5 years after initial treatment. Statistical analysis: Descriptive statistics will be calculated and multivariate models will be used where appropriate to adjust for potential confounders. In order to create and validate a prediction model, split validation and bootstrapping will be performed. Cost analysis will be carried out from the perspective of a national health system.

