## Background

Prevalence of breast cancer remains high worldwide [1]. Mortality rates have been decreasing since the 1970s. Screening programs and advences in adyuvant therapy have contributed to decrease mortality and this pathology has become in a chronic disease. l [2]. On the other hand, the development of new biomarkers and other diagnostic tools and new therapies could lead to a greater variability in clinical practice.

Several decision tools have already been created with the aim of predicting overall 5 or 10 year and disease-free survival [3–5]. In addition, with the increase in the life-expectancy in these women, it has become important to assess quality of life [6–8]. On the other hand, the course of breast cancer may be influenced by variables not directly related to the breast, such as other comorbidities and treatments [9–11].

This research was designed under the auspices of the Health Services Research on Chronic Patients Network (REDISSEC). This network was created to focus on three major issues: the challenge of managing the phenomenon of chronicity, the desire for more and better information, and a need to increase research capacity in the fields of health policies and services in Spain [12]. The overall objective of the CAMISS (abbreviation from the Spanish for health services research in breast cancer) research project is to evaluate the health services received by patients with breast cancer from screening, diagnosis and treatment to prognosis (complications, survival, and quality of life).

[name] et al. conducted the CAMISS-Retrospective study, which included 1086 women with breast cancer from a population-based screening program. These women were diagnosed with breast cancer between 2000 and 2008 and were followed-up to December 2013. The main objective of that study was to assess the impact of the mode of detection (screen-detected cancer vs. interval breast cancer) on overall survival and disease-free survival. Notably, however, symptomatic women were not included in this retrospective cohort and data were not collected on quality of life [13].

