### Variables

Reviewers in each hospital were provided with a handbook with instructions to follow in the data collection process.-Exposure variables:*Related to the patients’ personal background*: date of birth, sociodemographic variables (level of education, occupation of the patient or of the head of the household, marital status and living arrangements), height, weight, lifestyle habits, gynecological history (family history of gynecological cancer, oral contraceptives or hormonal replacement therapy, first and last menstruation date, menopausal status [pre- or postmenopausal], number of pregnancies and of births, breastfeeding [yes/no and duration]); and comorbidities (Charlson Comorbidity index) [16].*Related to the hospital*: number of beds, whether it is a teaching hospital, catchment population size, number of patients treated for breast cancer annually, and whether it has a breast cancer unit and medical or radiation oncology services.*Related to the process of care*: date of first contact with medical care (scheduled/emergency), time between the first symptoms and the first contact with medical services, time between the first medical appointment and histological diagnosis, time between diagnosis and treatment, and date of diagnosis.*Related to the pre-intervention tumor history*: mode of detection (symptomatic, screen-detected), symptoms (lump, lymph nodule, swelling or hardening of a part of breast, change in the size or shape of the breast, skin retraction, ulceration/wound, pain, secretion, inflammation, nipple retraction), date of the first symptom, clinical TNM classification (cTNM), additional diagnostic tests (ultrasound scan, magnetic resonance imaging [MRI], biopsy, computerized axial tomography [CAT], bone scan, galactography, ultrasound), histological type (infiltrating carcinoma, infiltrating ductal carcinoma, infiltrating lobular carcinoma, mucinous carcinoma, metaplastic carcinoma, intraductal carcinoma, and others) and serum marker levels (CA15-3, CA27.9, CEA, CA125).*Related to neoadjuvant treatment:* chemotherapy (regimen and whether it is completed), radiotherapy, hormone treatment, anti-HER2, and other therapies; and clinical and radiological response (assessed by MRI) categorized as no response (no changes or progression), weak partial response (if the tumor size reduced less than 50%), strong partial response (if the tumor size reduced by 50% or more), and complete response (no residual tumor) [17].*Related to surgery*: date, duration of the intervention, emergency vs scheduled, surgical technique (quadrantectomy, lumpectomy, segmentectomy, simple mastectomy, radical mastectomy, modified radical mastectomy, skin-sparing mastectomy, nipple-sparing mastectomy, contralateral prophylactic mastectomy, lymphadenectomy), time between diagnosis and intervention and/or pre-surgical adjuvant treatment, and intraoperative complications (bleeding, nerve injury, anesthetic complications, allergic reaction to the prophylactic antibiotic, others).*Related to anatomical pathology*: laterality, sentinel node biopsy (yes/no and results), histological type (intraductal, ductal, lobular, tubular, mucinous, medullary, cribriform, papillary, non-specific, others), degree of differentiation, pathological TNM (pTNM), location, size, distant metastases, vascular and nervous infiltration, number of lymph nodes analyzed and number positive, margin involvement, estrogen receptor/progesterone receptor status, Ki-67, P53, CK5/6, CK14, CK19, and HER2 expression, oncotype, and MammaPrint.*Related to admission*: setting (hospitalization vs. or ambulatory surgery), length of hospital stay in days after first intervention, in-hospital complications (seroma, wound infection, necrosis of skin flap, pneumothorax, brachial plexus pathology, and others), reintervention during admission, other medical treatments, and death.*Related to follow-up*: primary treatment: adjuvant postoperative treatment (radiotherapy, chemotherapy, hormone therapy, anti-HER2, and other therapy), date of treatments, reconstructive plastic surgery (yes/no, technique and date), other postoperative treatments (rehabilitation, psychologist/psychiatrist, others), and contact with social services; immediate complications and any reported during the follow-up period: chest wall and breast complications (seroma, post-surgery adhesions, soft tissue necrosis and recurrent skin infections), musculoskeletal (reduced arm mobility), lymphedema, neurological (paresthesias, neuropathy, cognitive dysfunction), pulmonary (pneumonitis, pulmonary fibrosis) cardiovascular morbidity (cardiomyopathy), psychological effects (anxiety), pain, other toxicities (ototoxicity, nephrotoxicity), reproductive health (premature menopause, infertility, sexual dysfunction), osteoporosis, weight gain, mycosis, and immunosuppression (agranulocytosis, lymphopenia); complications after reconstructive surgery (prosthesis infection, capsular contracture, others) and reinterventions, readmissions, death and their respective causes; and management of the disease during the follow-up period: diagnostic tests after surgery (CAT, positron emission tomography-CAT, biopsy, MRI, others), treatments (surgery, radiotherapy, chemotherapy, hormone therapy, anti-HER2, others), and number of follow-up visits per year (to the surgery/gynecology department, oncology department, rehabilitation unit, pain unit and palliative care unit).

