### Statistical analysis

- Descriptive statistics: Mean and standard deviations for continuous variables (or median and interquartile ranges, when the observed variables do not follow a normal distribution) and frequencies and percentages for qualitative variables.-Bivariate analysis:The Student’s t-test or the non-parametric Wilcoxon test (for non-normal distributions) will be applied for two-level outcomes, and ANOVA analysis or a Kruskal–Wallis test (for non-normal distributions) where there are three or more categories in the outcome. Otherwise, for categorical variables, the Chi-square test (or Fisher’s Exact method, where required) will be used. Multivariate models will be used where appropriate to adjust for confounders.-Creation and validation of predicitive models:. Participants will be randomly divided into two groups: the derivation (60%) and validation (40%) cohorts. The study unit will be the patient (each patient being included only once). The predictive model will be created with the derivation group (group 1). Initially, univariate analyses will be performed, to identify variables related to the selected outcomes. Variables with a *p* < 0.20 will be entered into a multivariate logistic regression model, when outcome variables are dichotomous (mortality, re-admissions or relapse, major complications). Statistically significant variables will be included in the final model. Based on its estimated contribution in the multivariate logistic regression model, a score will be assigned to each variable. From this, a severity risk score will be created with the receiver operating characteristic curve. One cut-off point will be selected, namely, that giving the best balance between sensitivity and specificity. For the continuous outcomes (changes in health-related quality of life), a general lineal model will be used. The validity of the model and the score will be tested in the validation sample (group 2) and also in the retrospective sample (group 3). We will calculate the sensitivity, specificity, and area under the receiver operating characteristic curve (AUC), and *p* values for comparisons of AUCs between the groups. The models will be calibrated using the Hosmer-Lemeshow test. A multilevel analysis will be performed with patients (level 1) nested within hospitals (level 2).

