### Expected outcomes of the study

The results of this coordinated project are expected to generate scientifically valid and clinically and socially important information to inform the decision-making of managers of screening programs, the authorities responsible for ensuring equality in the care process as well in health outcomes. For clinicians, clinical prediction rules will be developed which are expected to serve as the basis for software applications. Our intention is to create tools that will be easy to use, preferably to be added to electronic health records. This would allow physicians and patients themselves to consider the individual risk at the time of appointments, to guide their decisions. Such tools could also be used in evaluation of health services by health managers. Although here we describe in detail the protocol for 2 years of follow-up, our intention is to follow this cohort for longer (at least up to 5 years).

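### The 60/40 split is by patient within the same 13 hospitals, so the validation group is internal only and cannot show how the score performs in a new hospital

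*Protocol article*

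**What the plan says.** The Statistical analysis section of the protocol article builds the model in one random part of the cohort and checks it in the other: "Participants will be randomly divided into two groups: the derivation (60%) and validation (40%) cohorts". It fixes the unit: "The study unit will be the patient (each patient being included only once". Variables passing a univariate screen at p<0.20 go into a multivariable model, and the significant ones form the score.

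There is a second test: "The validity of the model and the score will be tested in the validation sample (group 2) and also in the retrospective sample (group 3". The Background describes that sample as the CAMISS-Retrospective study, "which included 1086 women with breast cancer from a population-based screening program", diagnosed from 2000 to 2008, without symptomatic women and without quality-of-life data. The paragraph closes with a two-level analysis of patients within hospitals, whose role in the score is not stated. The Abstract adds that "split validation and bootstrapping will be performed".

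The Variables section lists hospital characteristics among the exposures: "number of beds, whether it is a teaching hospital, catchment population size, number of patients treated for breast cancer annually", with breast unit and oncology services. Nothing in the Statistical analysis section keeps them out of the screen. Under Expected outcomes of the study, "clinical prediction rules will be developed which are expected to serve as the basis for software applications", and the Abstract speaks of risk tools for Spain.

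**The concern.** A random split of patients leaves practically every hospital in both groups. Whatever is peculiar to a hospital (its event rate, its case mix, its way of recording events) is then present both when the model is built and when it is checked.

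This matters most if hospital characteristics are screened as candidates. With 13 hospitals, a few such variables come close to identifying the hospital. A chance or local difference in event rate can be attributed to bed numbers or volume in the 60% and then appear confirmed in the 40%. The protocol itself expects hospital differences: Table 1 plans to study outcome variability by hospital, region and surgeon. Recording can also differ locally, because each hospital has its own reviewer and a record silent on complications is read as no complication.

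At stake is what the validation result means. A good AUC in the 40% would show that the score works for other women in the same hospitals. It would not show that it works in another Spanish hospital, which is where the software would be used.

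**Working it through.** **1. The plan's own figures (Sample size calculation).** 10 predictors × 10 events = 100 events; 100 / 0.07 = 1429, close to the 1456 valid patients. At the observed 4%: 1456 × 0.04 = 58.2 relapses; 58.2 / 10 = 5.8, the article's limit of six variables. Both reproduce.

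**2. What the split leaves.**
- Derivation: 0.60 × 1456 = 874 women; 874 × 0.04 = 35 relapses.
- Validation: 0.40 × 1456 = 582 women; 582 × 0.04 = 23 relapses.

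**3. Concentration (Table 2).** Basque Country: 197 + 246 + 125 + 229 + 245 + 134 = 1176; 1176 / 1456 = 80.8%.

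**4. Precision of the AUC in the 40%.** Hanley-McNeil: SE² = [A(1−A) + (e−1)(a−A²) + (n−1)(b−A²)] / (e·n), with a = A/(2−A), b = 2A²/(1+A), e = 23 events, n = 559 non-events. For A = 0.75: a = 0.600, b = 0.643, SE = 0.060, 95% half-width 1.96 × 0.060 = 0.117. Over A = 0.70 to 0.80 the half-width is 0.12 to 0.11.

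**5. Can shared hospitals inflate the AUC?** The documents give no between-hospital variance, predictor effects or final candidate list, so these are assumptions. Each simulation used the Table 2 hospital sizes, a random hospital intercept and a random 60/40 split, and scored the model both in the 40% and in unseen hospitals. The hospital-level variables had no true effect.

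*(a) Fixed model, 1500 runs per setting.* Three patient-level predictors (log odds ratios 0.7, 0.5, 0.4 per SD), with or without two hospital-level variables. AUC in the 40% minus AUC in unseen hospitals, 4% event rate:

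| Assumed ICC | Patient-level only | Plus two hospital variables |
|---|---|---|
| 0 | 0.000 | 0.004 |
| 0.02 | −0.001 | 0.008 |
| 0.05 | 0.001 | 0.016 |
| 0.10 | 0.001 | 0.028 |

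At 7% the first column stays at about 0 and the second runs from 0.003 to 0.025.

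*(b) The plan's selection applied (p<0.20, then p<0.05), up to 600 runs per setting.* Two patient-level predictors and six hospital variables, 4% event rate, all runs:

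| Assumed hospital SD (logit) | AUC in the 40% | AUC in new hospitals | Gap |
|---|---|---|---|
| 0 | 0.646 | 0.646 | 0.000 |
| 0.3 | 0.643 | 0.639 | 0.004 |
| 0.5 | 0.645 | 0.629 | 0.016 |
| 0.7 | 0.663 | 0.626 | 0.037 |

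At SD 0.5 a hospital variable entered the score in 39% of runs, and in those runs the gap was 0.651 − 0.606 = 0.045. At an event rate of about 20% (SD 0.5) the all-run gap was 0.675 − 0.643 = 0.032.

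*(c) A setting less favourable to the effect, 300 runs.* Four stronger patient-level predictors (AUC about 0.79) and hospital variables correlated at 0.6: gap 0.003 at SD 0.5 and 0.000 at SD 0.3.

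**6. Does the retrospective sample fill the gap?** It tests the relapse, mortality and complication rules in different women from an earlier period. It holds only screening-program women, so it cannot test the score in symptomatic women, who are part of the prospective cohort, and it cannot test the quality-of-life models at all. The article does not say which hospitals supplied it.

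**The case against.** The strongest reply is that the plan does not rest on the random split alone. It tests the score in the retrospective sample as well, compares AUCs between groups, plans a multilevel analysis and names bootstrapping. A reader might infer that the validation can only show that the score works in the hospitals where it was built. The documents do not support that: the retrospective sample is a separate test, and poor performance there would be a warning even if its cause could not be separated from era and case mix. What remains is that this sample covers only part of the target population and none of the quality-of-life outcomes.

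A reader might also infer that the reported AUC will be overstated. That does not follow. The excess arises only if the score carries hospital information. The hospital characteristics are listed as exposures for the whole study, and the article does not say that they are candidates for the score. With patient-level predictors unrelated to hospital the excess is nil, although calibration in a new hospital could still be off.

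The average excess is also small beside the sampling error from about 23 relapses, a half-width of 0.11 to 0.12. That is fair: the thin event count is a larger weakness of the split than the shared hospitals. But sampling error can be seen in a confidence interval, whereas shared-hospital optimism cannot be seen in group 2 at all.

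That the bootstrap is named in the Abstract and not described further is normal condensation in an article and is not held against the plan.

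**Conclusion.** The point holds in a limited form. The random 60/40 split is internal validation: it holds out no hospital, 81% of the women come from one region, and it gives no evidence of performance in a new hospital. The retrospective sample is a real additional test, but not for symptomatic women or quality of life.

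The numerical consequence is conditional. If hospital-level variables enter the score, the AUC can be overstated by roughly 0 to 0.03 on average at a 4% event rate under most of the variances tried (0.037 at the largest, SD 0.7). It is nil with patient-level predictors unrelated to hospital. These sizes rest on assumed between-hospital variances and predictor strengths. The larger gap of 0.045 applies only to runs in which a hospital variable was selected and should not be read as the expected bias. This is an inexpensive improvement to make, not a flaw that invalidates the study.

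**What to change.** Replace the random split with internal-external validation on the whole cohort:

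- Omit one hospital at a time, pooling small centres (for example Antequera, 6 women, with Costa del Sol, 80).
- Repeat the entire variable selection and score construction without the omitted hospital, then predict in it.
- Report discrimination and calibration pooled across hospitals.
- Use the bootstrap named in the Abstract, with selection repeated in each resample, to correct for optimism.
- Fit the final model on all 1456 women and keep the retrospective sample as an additional test.
- State whether hospital characteristics are candidates for the score.

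Omitting whole regions is a useful supplement for the three smaller ones. Omitting the Basque Country would leave 1456 − 1176 = 280 women and 280 × 0.04 = 11 relapses, too few to rebuild the model.

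This needs no new data and no longer divides about 58 relapses into 35 and 23. The costs are more computing, a rewritten paragraph and possibly a slightly lower reported AUC. Hospital-specific results cannot be interpreted singly: at 4% an omitted unit holds about 1 to 10 relapses (36 × 0.04 = 1.4; 86 × 0.04 = 3.4; 246 × 0.04 = 9.8). Since most hospitals are in one region, evidence for the rest of Spain would remain thin, and the report should say so.

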## Methods/Design

### Aim

The specific study objectives (which are set out in detail in Table 1) are, in brief: 1. to assess outcomes related to a) process of care (early diagnosis, access to health care and screening programs, delays in diagnosis, and variability in treatments), and b) patients (sociodemographic and clinical characteristics, including biomarkers, and patient-reported outcomes, such as quality of life and emotional state); 2. to create and validate prediction models (for changes in quality of life, relapse and death); and 3. to assess the costs associated with breast cancer care and its potential variations between Spanish regions.

**Table 1 Tab1:** Objectives

1. Outcomes assessment	2. Creation of predictive models	3. Health services evaluation in breast cancer patients in Spain
To describe and analyse variability in outcomes by mode of detection, hospital, region and surgeon	• To create and validate predictive rules for relapse, mortality and complications	• To estimate the average costs of breast cancer care in Spain
To describe and analyse variability in the diagnostic process and treatment	• To identify risk factors for poor health-related quality of life 2 years after treatment	• To investigate differences between Spanish regions
To explore potential inequalities by age, education and socioeconomic level	• To validate our predictive rules for relapse, mortality and complications in a retrospective sample of patients from early detection programs	• To identify the most efficient process and treatments in breast cancer
To evaluate the impact of first hospital care (urgent or scheduled) and of delays on relapse, metastasis and death		

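### The quality-of-life model is fitted in only 60% of the women, and the 40% held out gives little usable validation for a continuous outcome

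*Protocol article*

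**What the plan says.** All of this is in the protocol article.

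- **Split (Statistical analysis).** "Participants will be randomly divided into two groups: the derivation (60%) and validation (40%) cohorts". Models are built in the larger part only: "The predictive model will be created with the derivation group (group 1".
- **Quality of life in the same block.** After the logistic models and the risk score, and before validation is described, the text adds: "For the continuous outcomes (changes in health-related quality of life), a general lineal model will be used". No other analysis is named specifically for quality of life.
- **Validation.** "The validity of the model and the score will be tested in the validation sample (group 2) and also in the retrospective sample (group 3". The measures follow: "We will calculate the sensitivity, specificity, and area under the receiver operating characteristic curve (AUC", with p values comparing AUCs between groups and a Hosmer-Lemeshow test.
- **Objective (Aim).** The predictive-models column of Table 1 has a validation objective, "To create and validate predictive rules for relapse, mortality and complications", and a separate quality-of-life objective, "To identify risk factors for poor health-related quality of life 2 years after treatment". The Aim text above the table nevertheless lists change in quality of life, with relapse and death, among the prediction models to be both created and validated.
- **Retrospective cohort (Background).** It did not collect quality-of-life data.
- **Abstract, Methods.** "split validation and bootstrapping will be performed". The Statistical analysis section does not mention bootstrapping.

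**The concern.** A random hold-out has a price: the held-out women do not contribute to the coefficients. The price can be worth paying when the hold-out then tests the model. For quality of life, the article sets out the price but hardly any test.

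If the objective is the Table 1 one, identifying risk factors, the result wanted is an association with its confidence interval, and a hold-out is not needed for that. If it is the Aim-text one, a validated prediction model, the hold-out has a purpose. But the measures named do not fit a continuous change score, and the second validation sample lacks the outcome.

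At stake are wider intervals and a lower chance of detecting real risk factors, in data that have to be collected anyway. Two-year questionnaire response, which the article lists among its main anticipated problems, reduces the usable number further.

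**Working it through.** **1. The plan's own sample-size figures.** The Sample size calculation section asks for 100 relapse events at an expected 7%: 100 / 0.07 = 1429, close to the 1456 valid patients in Table 2. At the observed 4%, 1456 × 0.04 = 58.2 events, and 58.2 / 10 = 5.8, which is the stated limit of six variables. Both figures reproduce. Both concern relapse and use the whole sample; the section gives no calculation for quality of life.

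**2. Women contributing to the quality-of-life model.** 0.6 × 1456 = 874 in derivation and 582 held out, before non-response.

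**3. Loss of precision.** A standard error is proportional to 1/√n, so the ratio of derivation group to full cohort is √(1/0.6) = 1.29. Intervals are 29% wider whatever the response rate, provided response is similar in both parts of the random split.

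**4. Loss of power.** Two-sided 5% significance is assumed. If a factor has power Φ(δ − 1.960) in all women, it has Φ(δ√0.6 − 1.960) in the derivation group.

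| Power in all women | δ | δ√0.6 − 1.960 | Power in derivation group |
|---|---|---|---|
| 80% | 0.842 + 1.960 = 2.802 | 0.210 | 58% |
| 90% | 1.282 + 1.960 = 3.242 | 0.551 | 71% |
| 99% | 2.326 + 1.960 = 4.286 | 1.360 | 91% |

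The loss is largest for modest effects and small for strong ones.

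**5. Detectable differences, for illustration only.** For a binary factor with prevalence p, the difference detectable with 80% power is 2.80 / √(n p(1 − p)) in SD units. The article gives neither response rate, prevalence nor SD, so these are assumptions.

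| Assumed response | Assumed prevalence | All women | Derivation group |
|---|---|---|---|
| 100% | 50% | 0.147 SD (n = 1456) | 0.190 SD (n = 874) |
| 80% | 20% | 0.205 SD (n = 1165) | 0.265 SD (n = 699) |
| 60% | 10% | 0.316 SD (n = 874) | 0.408 SD (n = 524) |

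With an assumed SD of 20 points on the 0-100 scale, the middle row is 0.205 × 20 = 4.1 against 0.265 × 20 = 5.3 points.

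**6. What the hold-out returns for quality of life.**

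| Validation element named | Usable for a continuous change score? |
|---|---|
| Sensitivity, specificity | No; they need a dichotomous outcome |
| AUC and its comparison between groups | No; same reason |
| Hosmer-Lemeshow | No; it is a calibration test for a binary outcome |
| Group 2 (the 40%) | Outcome available, but no suitable measure is named |
| Group 3 (retrospective cohort) | No; quality of life was not collected |

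**The case against.** **The hold-out has a stated purpose.** A reader might infer from Table 1 alone that the split brings no gain at all for quality of life. The documents do not support that. The Aim text names change in quality of life among the models to be validated, the Table 1 objective stands in the predictive-models column, and group 2 is assigned to validation. The held-out women are therefore a validation sample, not discarded data. What stands is that the return is small as specified.

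**The risk-factor analysis might be done elsewhere.** Before the split is introduced, the section says in general terms that multivariable models will adjust for confounders where appropriate. A full-cohort quality-of-life analysis could be read into this. It is possible, but the sentence names no outcome, whereas the quality-of-life model is named inside the split block.

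**Bootstrapping may well be done.** It is tempting to say that it has been dropped. The Abstract says it will be performed, and an article may leave the details to a fuller plan. Its absence from the analysis section is an inconsistency and does not show that it is unused.

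**Selection by significance is not clearly stated for this outcome.** The p < 0.20 entry rule is tied to the logistic models, and the significance rule follows it there. It therefore cannot be asserted that quality-of-life factors will be screened in this way, or that the list will depend on one random split. Wider intervals and lower power follow in any case.

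**Split-sample validation is a recognised choice, and the derivation group is not small.** Both are true. The article gives no minimal important difference, so it cannot be shown that the change in detectable difference matters clinically. The argument is one of efficiency: the same women could yield tighter estimates at almost no cost.

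**Conclusion.** The point holds as an avoidable loss of efficiency together with two inconsistencies. As written, the quality-of-life model uses about 874 of 1456 women before non-response, with standard errors about 29% larger than in the full cohort and power falling from 80% to about 58%, or from 90% to about 71%. These ratios rest on the 60/40 split, similar response in both parts, and a two-sided 5% level. They apply to patient-level factors. For factors defined at hospital level, where the number of hospitals limits precision, the loss would be smaller. The differences in SD or points rest on assumed response, prevalence and SD and are illustrations.

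In return, the hold-out offers little for this outcome: no measure suited to a continuous score is named, and the retrospective cohort cannot be used. The two wordings of the objective and the unassigned bootstrapping need reconciling. The recommendation is the same under either reading of the objective: estimation needs no hold-out, and prediction can be validated internally on the full sample by a method the Abstract already names.

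**What to change.** 1. **Aim and Table 1:** state whether the quality-of-life objective is to estimate risk factors, to build a validated prediction model, or both, and use the same wording in both places.
2. **Statistical analysis:** take quality of life out of the 60/40 split. Fit the general linear model, with patients nested within hospitals as already planned, in all women with quality-of-life data, and report estimates with confidence intervals.
3. **If prediction is also wanted:** validate on the full sample with the bootstrapping named in the Abstract, repeat any variable selection in each resample, and report optimism-corrected R-squared and calibration slope. State that validation in the retrospective cohort does not apply to quality of life.
4. **Any detectable differences quoted:** label the response rate, prevalence and SD behind them as assumptions.

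The cost is a few sentences and modest computing, with no new data and no added burden on the women. The one small loss is that there is no separate random hold-out for quality of life. The handling of the binary outcomes is not affected by this change.
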